## **Objectives.** The purpose of this randomized controlled trial is to accomplish the following specific aims

**2**

Specific Aim 1: To quantitatively assess the effects of Isha yoga practices between seasoned practitioners and control groups on perceived stress, resilience, and wellbeing by use of validated scales.

Specific Aim 2: To compare protection and recovery from COVID-19 infection between seasoned Isha yoga practitioners and controls as demonstrated by:a.Self-reported duration of fever and respiratory symptoms in COVID-19 positive participantsb.Self-reported readiness to return to work (or a feeling of being physically and mentally fit)

Specific Aim 3: To compare prevalence rates of diagnosed COVID-19 infection between the seasoned Isha yoga practitioners and age and gender matched controls at baseline, 6 weeks and 12 weeks.

We hypothesize that routine yoga practice during the COVID-19 pandemic will reduce stress and enhance well-being.

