### Intervention description and timing

3.2

This is analytic study wherein an observational arm of ‘seasoned yoga practitioners’ is being compared with age, gender, and region matched ‘non-meditators’ as controls. The non-meditators control group is further randomized to active comparator arm and placebo comparator arm.

Control participants or Non-meditators are individuals with minimum (<1 month) to no yoga practice of any kind, prior to study enrollment. Non-meditator controls randomized to an ‘Active comparator arm’ are taught a 3 min yoga practice (Simha Kriya) which involves deep breathing exercises and meditation following randomization. Within the yogic tradition, there are breathing exercises which are considered to foster pranayama, which builds a type of “armor” or Kavacham for oneself against negative impacts encountered in the every day world. Prana is considered the fundamental energy and the foundation for all life. Pranayanic practices have been shown to contribute to positive physiologic and psychologic changes including improvements in hypertension, cognitive function, breathing frequency, stress, and heart rate variability [13,[32], [33], [34]]. In a study of another Isha pranayama practice, Peterson et al. found that after 6 weeks of daily practice, participants reported improved general well-being (General Well-Being Scale) and lower levels of perceived stress (Perceived Stress Scale) [35]. In the current study, the Simha Kriya practice will be taught on-line by highly-trained Isha practitioners and participants are asked to perform Simha Kriya using a web-based application, twice per day.

The other control group acts as a ‘Placebo comparator arm’ and performs either reading activities or remaining idle for 15 min a day throughout the study period. Respondents in the observational arm (seasoned yoga practitioners) continue their usual yoga practices. Please see Fig. 1 for study flow chart. Participants aged <18 years or >80 years will excluded from the study. Please see Table 1 for additional Inclusion/Exclusion Criteria.

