Aim 2 Analysis. To Compare Protection and Recovery from COVID 19 infection between seasoned Isha yoga practitioners and controls as demonstrated by:a.Self-reported duration of fever and respiratory symptoms in COVID-19 positive participantsb.Self-reported readiness to return to work (or a feeling of being physically and mentally fit)

We will calculate the protection and recovery rates from COVID-19 infection as defined by the aforementioned criteria. Given the continuous nature of the criteria used to assess symptom duration and sense of recovery, differences between groups will be assessed in a univariable manner with a parametric or non-parametric *t*-test. We will perform spot analysis at the three defined points to capture the point prevalence of recovery rates. We also intend to assess the differences between the prevention and recovery rates at baseline and six weeks and baseline and twelve weeks. We will employ the mixed model technique similarly to the analysis suggested in the aim #1 analysis.

Analysis of Aim 3: To compare Prevalence rates of diagnosed COVID-19 infection between the seasoned Isha yoga practitioners and age and gender matched controls at baseline, 6 weeks, and 12 weeks.

We will compute period prevalence of diagnosed COVID-19 infections as a measure of frequency. Since the data to be analyzed are not dependent on duration, we intend to compute the prevalence rates at the following time points: baseline, 6 weeks, and 12 weeks. The result would be reported as the portion of study population with COVID-19 at the specified time point.

Finally, we will perform an exploratory analysis of the data collected by comparing the effect of yoga practices and their duration between the 3 study groups to estimate a dose-response trend if possible.

Compliance is defined as 3 days of activity each week for at least 3 weeks from baseline to 6 weeks, or a minimum of 6 weeks from baseline to 12 weeks. Measures of frequency and association will also be calculated. We will complete exploratory analysis by comparing the different yoga practices and their duration between the 3 study groups to assess a dose-response pattern.

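### Aim 2 defines a COVID-19 protection rate by criteria that cannot show who avoided infection, and duration among cases is conditional on an event the study expects yoga to change

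*Protocol article*

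**What the plan says.** The Objectives section gives Specific Aim 2 as "To compare protection and recovery from COVID-19 infection between seasoned Isha yoga practitioners and controls as demonstrated by" two self-reported criteria. The Analysis section (3.6) repeats them: (a) "duration of fever and respiratory symptoms in COVID-19 positive" participants, and (b) "Self-reported readiness to return to work (or a feeling of being physically and mentally fit"). It continues: "We will calculate the protection and recovery rates from COVID-19 infection as defined by the aforementioned criteria". For symptom duration and sense of recovery, "differences between groups will be assessed in a univariable manner with a parametric or non-parametric" t-test. Then: "We also intend to assess the differences between the prevention and recovery rates at baseline and six weeks and baseline and twelve weeks". Prevention gets no definition of its own. The Aim 2 paragraph ends by calling for a mixed model like that of Aim 1.

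Aim 3, in the same section, covers diagnosed infection in everyone: "The result would be reported as the portion of study population with COVID-19 at the specified time point". The text does not link this to the Aim 2 protection rate.

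The Abstract and Discussion both hypothesise that yoga protects against COVID-19.

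**The concern.** There are two separate problems.

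The first is definitional. A protection rate needs a denominator of people at risk and a count of those who stayed free of infection. Criterion (a) drops everyone who stayed free. Criterion (b) has no stated population and measures fitness on any reading. The article fixes this definition itself, so it is not a detail left to a fuller plan.

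The second is selection. Duration can be seen only in people who became diagnosed cases, and the study expects yoga to change who those are. If it changes the mix of mild and severe illness among cases, a difference in mean duration reflects that mix as well as any effect on recovery.

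At stake is a published statement about protection from COVID-19 resting on data that cannot bear on it, or a recovery result with the wrong sign.

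**Working it through.** **Inputs.** The article gives no infection risk, illness duration or sample size for Aim 2, so there is no figure to reproduce. All numbers below are assumptions chosen to show direction and rough size.

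**Step 1: is the measure blind to protection?** Assume 70% robust people (5 symptom days if infected), 30% frail people (14 days), and a control infection risk of 6% in both.

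- Days per enrolled person = sum of share × risk × duration.
- Days per case = that sum ÷ (sum of share × risk).
- Controls: 0.7×0.06×5 + 0.3×0.06×14 = 0.210 + 0.252 = 0.462 days per person, and 0.462/0.06 = 7.70 days per case.
- Uniform risk ratio 0.5: 0.231/0.030 = 7.70 days per case.
- Uniform risk ratio 0.1: 0.0462/0.006 = 7.70 days per case.

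Infections fall from 6.0% to 3.0% or 0.6%, and duration among cases stays put.

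**Step 2: can the sign reverse?** Let practice prevent infection in robust people only, with no effect on duration. At risk ratio 0.4, infected = 0.7×0.024 + 0.3×0.06 = 0.0348, and days = 0.0168×5 + 0.018×14 = 0.336.

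| Risk ratio, robust only | Days per case | Days per enrolled person |
|---|---|---|
| 1.0 | 7.70 | 0.462 |
| 0.8 | 8.14 | 0.420 |
| 0.6 | 8.75 | 0.378 |
| 0.4 | 9.66 | 0.336 |
| 0.2 | 11.14 | 0.294 |

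Now add a true shortening of 0.5 days for every case:

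- Risk ratio 1: 7.20 v 7.70, which is correct.
- Risk ratio 0.8: 7.64 v 7.70, nearly null.
- Risk ratio 0.4: 9.16 v 7.70, apparent harm, although days per enrolled person fall from 0.462 to 0.319.

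**Step 3: the opposite direction.** With risk ratio 0.4 in frail people only and no effect on duration, infected = 0.042 + 0.0072 = 0.0492 and days = 0.210 + 0.1008 = 0.3108. That gives 6.32 days per case against 7.70, so recovery looks faster when no illness was shortened.

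**Step 4: a second model.** Take lognormal duration with median 10 days and log-SD 0.8, so the mean is 10×exp(0.8²/2) = 13.77. If the shortest fraction p of illnesses is prevented, the share of symptom days kept is Φ(0.8 − z_p), and the mean among remaining cases is 13.77 × Φ(0.8 − z_p)/(1 − p).

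- p = 0.1: 13.77×0.9813/0.9 = 15.0 (+9%).
- p = 0.2: 13.77×0.9497/0.8 = 16.35 (+19%), and total symptom days fall by 1 − 0.9497 = 5%.
- p = 0.3: 13.77×0.9073/0.7 = 17.8 (+30%).
- Preventing a random 20%: the mean stays at 13.77 (0%), and total days fall 20%.

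**Step 5: does the mixed model help?** Under Aim 1 it gives each cluster of friends or matched subjects a random intercept. That handles correlation. It does not bring back the people absent from the case set. Covariate adjustment, which Aim 1 makes optional, removes only the selection carried by measured factors.

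**The case against.** The strongest reply is that the defect is largely a label. Aim 3 measures diagnosed infection in all participants. Perceived stress is primary and resilience key secondary, so Aim 2 is neither. The Introduction also describes an earlier study of preventive effects on incidence, duration and severity together, so the article's use of protection may loosely include milder illness. Aim 3 and the lower rank of Aim 2 limit the damage. But Aim 2 names protection alongside recovery, announces a rate for it, and ties that rate to criteria that count no avoided infections.

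Some stronger readings are tempting and are not supported:

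- *Preventing infections will make yoga look harmful.* This holds only if prevention is concentrated in short or mild illness. Even prevention leaves duration among cases unchanged, and preventing long illness flatters yoga.
- *The unadjusted t-test is the whole analysis.* The same paragraph plans a mixed model as well.
- *Selection destroys the randomisation behind Aim 2.* The stated contrast is practitioners against controls, and the article says "This is analytic study wherein an observational arm of ‘seasoned yoga practitioners’ is being compared with age, gender, and region matched" non-meditators. It was never randomised. The point reaches the two randomised control arms only if Aim 2 is also compared between them, as the article's later move to three groups could imply.
- *Few infected practitioners will have an infected matched control, so matching fails.* The planned t-test compares groups. Few intact pairs do not by themselves unbalance groups; differential selection is needed.
- *Symptom days in all participants should replace Aim 2.* That outcome mixes incidence with recovery, needs symptom timing the article does not confirm was collected, and would be post hoc, since the article says amendments followed review of the data.

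**Conclusion.** The definition of the protection rate is wrong as written: followed literally, it yields a result labelled protection that contains no information on avoided infection. This needs no assumption beyond the text.

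The selection concern is real but conditional. It requires that practice affect infection or diagnosis differently by illness severity. If so, the distortion can be material: +9% to +30% in mean duration among cases when the shortest 10% to 30% of illnesses are prevented, zero under random prevention, and the reverse sign when long illnesses are prevented. The direction in this study cannot be known from the article. Neither the cluster intercepts nor optional adjustment can be relied on to remove it.

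**What to change.** 1. Delete protection and prevention from Aim 2 in the Objectives and Analysis sections.
2. Assess protection only through diagnosed infection in all participants under Aim 3, ideally as new diagnoses after baseline among those not infected at baseline. For practitioners this remains an observational contrast.
3. Keep duration and readiness among cases as a recovery measure, adjusted for age, gender and medical history. State that it is conditional on infection and do not describe it as an effect of yoga.
4. If symptom timing was collected, symptom days per enrolled participant (zero for those without a COVID-19 illness) may be added as a supplementary burden measure, labelled post hoc.

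The cost is wording, plus an adjusted model using medical history that the surveys already collect. Aim 2 will support a weaker conclusion, and the burden measure, if used, will have many zeros and needs a rank-based, two-part or bootstrap comparison.

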### Data collection

3.3

Participants will be asked to complete a series of web-based surveys at baseline, six weeks and 12 weeks. These surveys include validated scales and objective questions on COVID-19 infection and medical history. The validated questionnaires assess stress, mood states, resilience, and overall wellbeing. Questionnaires, weekly activity diaries, and medical history, will be collected using REDCap. All surveys will all be automated and the study team will have minimal interaction with the participants. All health information provided by the participants is self-reported.

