### Analysis

3.6

Baseline characteristics of participants will be recorded. Continuous data will be presented as means ± standard deviation or median (interquartile range) depending on the distribution of the data and assessed with a parametric paired *t*-test or non-parametric Wilcoxon signed rank test, as appropriate. Normality will be assessed with the Shapiro-Wilk test. Categorical data will be presented as frequencies and percentages and assessed with a chi-square or Fisher's exact test, as appropriate. All primary analyses will be assessed using intention-to-treat principles. SAS 9.4 (SAS Institute Inc., Cary, NC) will be used for all analyses with two-sided p-values < 0.05 considered statistically significant.

Aim 1 Analysis. To quantitatively assess the effects of Isha yoga practices between seasoned practitioners and the control groups on measures such as perceived stress, resilience, and overall wellbeing by use of validated scales at baseline, 6 weeks and 12 weeks. We have defined Perceived Stress Score as our primary outcome and Brief Resilience Scale scores as our key secondary outcome. Given the continuous nature of the scales used to assess stress, resilience and measures of well-being, differences between groups will be assessed with a parametric or non-parametric *t*-test. Multivariable regression may be utilized to adjust for potential confounders that deem to vary between the groups based on the univariable analysis prior to that. The distribution of the dependent variable will depend on the actual distribution of the scales recorded in the study. A mixed effect approach in modeling will address the similarity of the subjects enrolled in the study as friends or by matching, by assigning a random intercept to each cluster of related subjects. To assess whether there are differences between baseline and at six weeks, we will employ the use of paired t-tests or non-parametric tests for univariable analysis, as appropriate. Additionally, the change in scales over time can be compared between the groups using mixed models approach, wherein an indicator of time (baseline/6 weeks) will define the direction and significance of the change in a model, adjusted independent of other factors.

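### Aim 2 cannot yield a protection rate from its two criteria, and its t-test for symptom duration has no place for illness unresolved at the last survey

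*Protocol article*

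**What the plan says.** Aim 2 (protocol article, Objectives, repeated in section 3.6 Analysis) is to compare protection and recovery from COVID-19 between seasoned practitioners and controls. It lists two criteria. The first is the self-reported duration of fever and respiratory symptoms, limited to COVID-19 positive participants. The second is "Self-reported readiness to return to work (or a feeling of being physically and mentally fit".

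Section 3.6 then sets out the analysis:

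- Definition of the rates: "We will calculate the protection and recovery rates from COVID-19 infection as defined by the aforementioned criteria".
- Data type and comparison: "Given the continuous nature of the criteria used to assess symptom duration and sense of recovery, differences between groups will be assessed". The test named is a univariable t-test, in either its parametric or its non-parametric form.
- Recovery by time point: "We will perform spot analysis at the three defined points to capture the point prevalence of recovery rates".
- Change from baseline: prevention and recovery rates at baseline are to be compared with those at six and at twelve weeks, and "We will employ the mixed model technique similarly to the analysis suggested in the aim #1 analysis".

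Section 3.3 Data collection fixes when participants are observed: "Participants will be asked to complete a series of web-based surveys at baseline, six weeks and 12 weeks". Infection frequency in the whole study population appears only under Aim 3, as prevalence of diagnosed COVID-19.

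**The concern.** There are three difficulties, in order of certainty.

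1. **Protection.** A protection rate needs new infections over a denominator of people at risk. Neither criterion supplies this. The Abstract and the Discussion hypothesise protective effects against COVID-19, so a protection result reported under Aim 2 would support a prominent claim with data that cannot inform it.

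2. **Duration.** A participant still ill at the last survey has a right-censored duration. A t-test or a rank test on the recorded values must either take the duration so far as final or leave the case out. Both remove the long end of the distribution, and remove more of it in the group with longer illness, so the groups look more alike than they are.

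3. **Change from baseline.** The Aim 1 mixed model suits scales that every participant answers at each survey. Symptom duration exists only for those infected, and that set changes between surveys. A contrast of duration at baseline with duration at 6 or 12 weeks is therefore largely between different people, and infections before baseline precede the activity assigned to the controls.

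**Working it through.** **Protection: reading the text**

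| Criterion | Who contributes | What it measures | Infections over people at risk? |
|---|---|---|---|
| Duration of fever and respiratory symptoms | COVID-19 positive participants | Length of illness | No |
| Readiness to return to work, or feeling fit | No restriction stated | Recovery or fitness | No |
| Aim 3: diagnosed COVID-19 | All participants | Infection frequency | Yes, as prevalence |

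The first two rows are the only criteria to which the definition of the rates can refer. This part needs no numerical assumption.

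**Duration: size of the bias if unresolved cases occur**

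The article states no symptom duration, event count or unresolved share, so there is no figure of its own to reproduce. The one input from the document is the end of observation, 12 weeks, so W = 84 days. Assumed: onset uniform over the 84 days, and exponential duration with mean m.

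- Share unresolved at W: p = (m/W)(1 − e^(−W/m))
- Mean if the duration so far is taken as final: T = m(1 − p)
- Part of T contributed by unresolved cases: G = (m²/W)[1 − (1 + W/m)e^(−W/m)]
- Mean if unresolved cases are dropped: R = (T − G)/(1 − p)

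Example, m = 14: p = (14/84)(1 − e^(−6)) = 0.166; T = 14 × 0.834 = 11.67; G = 2.29; R = (11.67 − 2.29)/0.834 = 11.25.

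| Mean m (days) | p | T | R |
|---|---|---|---|
| 5 | 6.0% | 4.70 | 4.68 |
| 7 | 8.3% | 6.42 | 6.36 |
| 10 | 11.9% | 8.81 | 8.65 |
| 14 | 16.6% | 11.67 | 11.25 |
| 21 | 24.5% | 15.85 | 14.68 |

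Differences between groups:

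| True means | True difference | Duration so far as final | Unresolved dropped |
|---|---|---|---|
| 7 v 5 | 2 days | 1.71 (−14%) | 1.68 (−16%) |
| 14 v 10 | 4 days | 2.86 (−28%) | 2.60 (−35%) |
| 21 v 14 | 7 days | 4.17 (−40%) | 3.43 (−51%) |

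**Sensitivity to the distribution.** A simulation with lognormal durations (log-SD 0.8, 2,000,000 per arm, onset uniform over 84 days) gave shrinkage of 18–19% for medians of 5 v 7 days, 35–37% for 10 v 14 and 58–60% for 20 v 28. The direction does not depend on the exponential form; the size depends on how long illness lasts. As the unresolved share falls to zero, so does the bias.

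**The case against.** - **The bias is conditional.** It needs unresolved cases, and the article gives no data on how many to expect. This stands. A reader might infer that recovery times will certainly be biased, or biased by half; the document supports neither.
- **Earlier infections may dilute it.** The text does not limit positive participants to new infections, and most illnesses before enrolment would have complete durations. This also stands: the calculation places every onset inside the 84 days.
- **Handling rules may be in a fuller plan.** They may be, and their absence here is not the point. The method that the article does name cannot use a censored duration. The non-parametric option does not change that, nor does the mixed model as described.
- **Not every Aim 2 analysis is affected.** Correct. In the point prevalence of recovery, an unresolved case can count as not recovered.
- **Protection is only mislabelled, since Aim 3 covers infection.** Largely so, which makes the correction cheap. But the text returns to prevention rates in the change-from-baseline analysis, so it is more than a single slip.

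Two further readings go too far. One is that both criteria are restricted to infected people: only the first says so. The other is that readiness to return to work cannot be continuous: the questionnaire item is not shown, and a time to readiness would be continuous. What can be said is that the article gives no scale, unit or time origin to support calling it continuous.

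**Conclusion.** The point holds in two parts. A protection or prevention rate cannot be computed from the Aim 2 criteria; this follows from the text alone. The method named for comparing durations is the wrong type where illness is unresolved at the last survey. If such cases occur, the group difference shrinks by about 14–16% for means of 7 v 5 days and 40–51% for 21 v 14 days, assuming uniform onset over 84 days and exponential durations. A baseline v 6- or 12-week contrast of duration has the further fault of comparing largely different infected people.

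A reader might also describe Aim 2 as conditioning on infection after randomisation. That does not fit the design: under sections 3.2 and 3.5 the seasoned practitioners are an observational arm and only the controls are randomised. The reasons to treat Aim 2 as descriptive are that the duration comparison is restricted to infected participants and that the practitioner arm is not randomised.

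The Perceived Stress Scale is the primary outcome and the Brief Resilience Scale the key secondary, so neither of those conclusions changes. Severity is low to moderate.

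**What to change.** - Remove protection and prevention from Aim 2, and draw any such conclusion from Aim 3 only.
- Compare symptom duration by Kaplan-Meier with Cox regression or restricted mean time, censoring unresolved cases at the last survey. Keep a cluster term (frailty or robust variance) for friend or matched sets, since otherwise the random intercept of the Aim 1 model is lost.
- Treat readiness to return to work in the same way if it was recorded as a time. If it was recorded as a yes/no state, compare proportions.
- Separate infections before enrolment from those after it, and drop the change-from-baseline model for duration. Keep the point prevalence of recovery.
- Label Aim 2 descriptive.

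The cost is mostly wording, with one condition. The surveys must have recorded duration together with whether the participant was still ill. A duration alone gives no onset date, and the article does not say that dates were collected. Section 3.6 reports that the 12-week data had already been reviewed, so a missing item cannot now be added through the analysis plan. Events may be few and intervals wide.

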*Brief Resilience scale (BRS).* The BRS identifies an individual's ability to “bounce back” or recover from a stress. This 6-item scale is rated on a 5-point response scale (1 = Strongly disagree; 5 = Strongly agree). Responses from each of the 6 questions are summed to create a total score, producing a range of 6–30. The score is divided by the number of questions answered to calculate the individual brief resilience score.

*Warwick- Edinburgh Wellbeing Scale (WEMWBS).* The purpose of the WEMBS scale is to assess various aspects of mental health such as positive affect, satisfying interpersonal relationships, and positive functioning. This 14-item scale is rated on a 4-point response scale (1 = none of the time to 4 = all of the time). Response from each of the 6 questions is then summed to create a total wellbeing score.

*Post Traumatic Growth Inventory (PTGI).* The purpose of the PTGI is to capture the positive outcomes reported by a person who has experienced a traumatic event. This scale will be administered only to those participants who report being hospitalized during the COVID-19 pandemic. The scale helps to determine a respondent's coping ability in the aftermath of a trauma, their perceptions of self and others, and meaning of the event. This 21-item scale is rated on a 6-point Likert response scale and response to each question is summed to create a total PTGI score.

*Activity Diary.* The weekly activity diary is a tool which helps the participants to keep a track of their activities each week. This enables the study team to measure compliance and protocol adherence by the participants. Based on the construct of the study, we have 2 different activity diaries employed for data collection in this study. The activity diary for seasoned yoga practitioners collects information on their routine activity practiced, its frequency and duration. The activity diary for controls collects information on the activity suggested by study team (the Simha Kriya yoga practice vs placebo activity choices of reading or remaining idle).

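### Aim 2 compares symptom duration by t-test as if every illness had ended; open episodes shorten recorded durations, shrink true differences and, where infection timing differs between groups, can mimic faster recovery

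*Protocol article*

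**What the plan says.** Aim 2 has two self-reported recovery outcomes: how long fever and respiratory symptoms lasted in infected participants, and "Self-reported readiness to return to work (or a feeling of being physically and mentally fit". In the Protocol article, section 3.6 Analysis, the choice of test is justified as follows: "Given the continuous nature of the criteria used to assess symptom duration and sense of recovery, differences between groups will be assessed". The sentence then names the comparison to be made: "in a univariable manner with a parametric or non-parametric *t*-test".

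Two further Aim 2 analyses follow. One is a snapshot of recovery: "We will perform spot analysis at the three defined points to capture the point prevalence of recovery rates". The other is a model carried over from Aim 1: "We will employ the mixed model technique similarly to the analysis suggested in the aim #1 analysis". As described for Aim 1, that model has a random intercept per cluster of related participants and an indicator of time. It has no element for incomplete durations.

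On sources, section 3.3 Data collection says "Participants will be asked to complete a series of web-based surveys at baseline, six weeks and 12 weeks" and "All health information provided by the participants is self-reported". The only more frequent instrument is the diary in section 3.4: "The weekly activity diary is a tool which helps the participants to keep a track of their activities each week". It is described as a measure of compliance, not of symptoms.

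**The concern.** Duration takes continuous values, but it is known in full only once the illness has ended. For someone still symptomatic when answering, the survey shows only that the illness has lasted at least so many days. A t-test or rank test needs one finished number per person. That leaves two options, both of which lose long illnesses: enter the days so far, or leave the person out.

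Two consequences follow.

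- **Attenuation.** Longer illnesses are the likelier ones to be open at a survey, so the slower-recovering group is cut more. A real difference shrinks, even when both groups were infected at the same times.
- **False difference.** The amount cut also depends on how long before the survey people fell ill. If one group's infections cluster nearer the survey, its recorded durations are shorter with no difference in recovery. The Discussion (section 4) itself says the epidemic moved at different rates in different regions.

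Recovery is a named specific aim, and protection against COVID-19 is part of the stated hypothesis, so a misleading duration result would bear on a claim the trial intends to make.

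**Working it through.** The article gives no infection count, symptom duration or power for Aim 2, so there is no figure of the plan to reproduce. What follows illustrates the mechanism.

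**From the article:** surveys 42 days apart; two-sided 0.05; t-test or its non-parametric counterpart.

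**Assumed:** duration D lognormal, median 10 days, log-SD 0.8; all onsets within one 42-day interval; 40 (or 20) infected per group. G is the time from onset to survey.

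**Step 1, true mean.** 10 × exp(0.8²/2) = 10 × exp(0.32) = 13.8 days.

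**Step 2, share still ill, onsets uniform.** P(D > G) = E[min(D, 42)]/42.
- E[min(D, 42)] = 13.77 × Φ((ln 4.2 − 0.64)/0.8) + 42 × (1 − Φ(ln 4.2/0.8)) = 13.77 × 0.840 + 42 × 0.0364 = 13.1.
- 13.1/42 = 31%.

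**Step 3, recorded mean, onsets uniform (simulated).** 9.9 days if days so far are entered and 9.6 if the still-ill are dropped, against a true 13.8.

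**Step 4, attenuation with equal timing.** Let the other group have median 7.5 days, so its true mean is 7.5 × exp(0.32) = 10.3 and the true difference is 13.77 − 10.33 = 3.4 days. With uniform onsets in both groups:
- days so far: 9.86 − 8.04 = 1.8 days;
- still-ill dropped: 9.62 − 7.89 = 1.7 days.

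About half the true difference is lost.

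**Step 5, false difference with unequal timing.** Same D in both groups. For infections doubling every T days, the density of G is proportional to 2^(−g/T); for halving, to 2^(g/T). With 14-day doubling in one group and 14-day halving in the other, the recorded means are 7.9 and 11.4 days, a false gap of 3.5 days. If the still-ill are dropped they are 8.5 and 10.5. False-positive rates, 6,000 runs each:

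| Onset timing | t-test, days so far, n = 40 | rank-sum, days so far, n = 40 | t-test, still-ill dropped, n = 40 | t-test, days so far, n = 20 |
|---|---|---|---|---|
| same (uniform) | 6% | 5% | 5% | 5% |
| 28-day doubling vs uniform | 10% | 10% | 5% | 7% |
| 14-day vs 28-day doubling | 10% | 10% | 6% | 7% |
| 14-day halving vs uniform | 15% | 14% | 8% | 10% |
| 28-day doubling vs 28-day halving | 19% | 19% | 8% | 12% |
| 14-day doubling vs uniform | 25% | 25% | 8% | 14% |
| 14-day doubling vs 14-day halving | 56% | 57% | 16% | 32% |

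A separate run of 3,000 simulations gave 9% for the second row, hence the rounded range of 9 to 25% for moderate differences. The rank test gives no protection, because it ranks the same shortened values.

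**Step 6, different assumptions.** Gamma durations (coefficient of variation 0.6), equal in both groups, 50 infected per group, days so far entered:
- uniform versus late-weighted onset: t-test false positives 13%, 32% and 49% for true means of 7, 14 and 21 days;
- early- versus late-weighted onset: 36%, 84% and 98%;
- same timing: about 5%.

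A log-rank test with open episodes censored at the survey stayed between 3.0% and 7.4% over all scenarios (500 runs each, simulation error about 1 point). The size therefore depends heavily on the assumptions. The mechanism, and its removal by censoring, do not.

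**Step 7, if open week-6 episodes are completed at week 12.** The window becomes 84 days. At a gamma mean of 14 days with uniform onset, the share cut falls from 33% to 17%.

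**The case against.** The strongest reply is that the text fixes less than a critical reader may infer. Much of that reply stands.

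- *The t-test is run on partial durations at every survey.* The article does not say so. It ties the three survey points to the prevalence of recovery. It does not say what is entered for someone still ill, and the same people are asked again at week 12, so an episode open at week 6 could be completed then. A full analysis plan or survey form may contain such a rule, and its absence from a journal article is not a fault. What remains is the stated rationale and test, which have no place for an episode that has not ended, and some can still be open at week 12.
- *The extreme false-positive rate is what to expect.* It is not. It needs opposite epidemic phases in the two groups, whereas controls are preferably from the same neighbourhood and fallback matching starts at zip code. Matching limits timing differences without removing them: it can fall back to county or state, and nominated controls enrol after the practitioner who names them.
- *All comparisons are equally affected.* They are not. The two control arms are randomised, so their infection timing differs only by chance and the test keeps its level.
- *The direction of bias is unknowable.* It is not. With equal timing, differences shrink; with unequal timing, the later-infected group looks faster. Onset dates, if collected, would show which applies.

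The outcome is also neither primary (PSS) nor key secondary (BRS), and it concerns infected participants only. That limits the weight of the point, not its correctness.

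**Conclusion.** The concern holds in a limited form. Section 3.6 chooses a test for complete values and applies it to an outcome that is right-censored for anyone still ill when last surveyed.

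The firm part is understated duration and attenuation, which need no difference in timing; under the assumed lognormal model about half of a 3.4-day difference is lost. The conditional part is a false recovery advantage in the non-randomised practitioner-versus-control comparison. It is absent with equal timing, moderate in plausible cases and large only in extreme ones. Between the randomised arms the main harm is attenuation.

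Every size rests on assumed durations, onset patterns and infection counts, and on a 42-day window; completing open episodes at week 12 would reduce it. The documents do not support saying that the recovery result must be false, or that it must favour yoga. The point is confined to symptom duration, because the article does not describe how readiness to return to work is recorded.

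**What to change.** Replace the duration t-test, and the mixed model as far as it applies to duration, with one time-to-event analysis:

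- outcome: time from symptom onset to resolution, one episode per person;
- link an episode open at one survey to the next, and censor it at the last completed survey if still unresolved;
- describe by Kaplan-Meier, and compare by a Cox model or restricted mean time that respects the matched clusters;
- report the randomised comparison of the control arms separately from the comparison with practitioners.

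Section 3.6 indicates that the 12-week data have already been collected and reviewed, so the repair is a re-analysis using onset and end dates where the surveys recorded them. If they did not, state the limitation and make no claim about recovery duration. The prevalence of recovery at each survey is a different quantity and may stay as a description.

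The cost is a little more analysis work on a non-primary outcome, using standard procedures.
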